Does learning the Bhagavad Gita provide any added benefit to people experiencing homelessness who are engaging in a recreational activity in terms of reducing their psychological distress	The decrease from baselines to immediately post-intervention, delayed post-intervention, and long-term follow-up Kessler psychological distress scale scores will be significantly larger in the Both group than the Bhagavad Gita and Kuchipudi dance groups	54 participants each in the Bhagavad Gita group, Kuchipudi dance group, Both Bhagavad Gita and Kuchipudi dance group, and Control group for 80% power and 5% alpha	Intergroup differences will be analysed by the generalised estimating equation and analysis of covariance with continued practice and religion as covariates. Subgroup analyses will be conducted by stratifying the participants in each group by age, religion (Hindu, Non-Hindu), educational attainment, and employment. Post-hoc power analyses will be conducted to verify the robustness and reliability of the subgroup analyses	If the reduction in the Kessler psychological distress scale scores is highest in the Both group, it would suggest that learning the Bhagavad Gita combined with engaging in a recreational activity may offer additional benefits in reducing psychological distress among homeless persons compared to learning the Bhagavad Gita group or engaging in a recreational activity alone. This finding would indicate that the combination of the intervention has a more substantial effect on decreasing distress levels

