### Statistical methods

#### Data analysis

All results will be reported in accordance with the CONSORT guidelines to ensure comprehensive and transparent reporting of the trial’s outcomes. Descriptive summaries of baseline characteristics will be presented to provide an overview of the study population. The comparisons will be between each intervention group and the control group, as well as within each intervention group over time. The repeated measures data will be analysed using the generalised estimating equation (GEE) framework. For the analysis of the primary outcome using the GEE framework, robust standard errors will be used to account for correlated data. Pairwise post-hoc comparisons will be conducted to identify specific group differences. To control for the risk of type I error in these multiple comparisons, the Bonferroni correction will be applied. Subgroup analysis will be conducted using analysis of covariance (ANCOVA) or non-parametric ANCOVA [19] depending on the normality of the data; this may include stratification by age, educational attainment, religion, and employment status. Multiple comparisons will also be addressed using appropriate statistical corrections. These may include the Bonferroni correction, Holm’s adjustment, or the Benjamini-Hochberg procedure, depending on the specific comparisons and the number of tests conducted. The data analysis will be conducted using Python 3.9.13. Statistical significance will be set at a two-tailed p < 0.05.

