#### Sample size calculation

The required sample size for GEE was calculated using the formula,

$$n=[(Z\alpha /2+Z\beta {)}^{2}*V\_eff]/(\Delta^{2}*\rho^{2}),$$

where n is the required sample size per group; Zα/2 is the critical value of the standard normal distribution for a two-tailed test with a significance level of α; Zβ is the critical value of the standard normal distribution for a specified power (1-β) of the test; V_eff is the effective sample size, which accounts for the correlation between the repeated measures within individuals; Δ is the minimum clinically significant difference; r is the number of repeated measures; and ρ is the correlation between the repeated measures.

Assuming a conservative value of 0.5 for ρ based on previous literature [20, 21], and for an α of 5%, 1-β of 80%, r of 4, and Δ of 7 [22, 23], we can calculate the effective sample size as follows:

$$\begin{array}{l} V\_eff=n/(1+(r‐1)*\rho )\\ \;=55/(1+(4‐1)*0.5)\\ \;=22.5 \end{array}$$

Therefore, n can be calculated as follows:

$$\begin{array}{l} n=[(1.96+0.84{)}^{2}*22.5]/(7^{2}*0.5^{2})\\ \;=53.3 \end{array}$$

Thus, at least 54 participants per group must be enrolled to have 80% power to detect a minimum clinically significant difference of 7 points between the groups using GEE, with a significance level of 5%. As there are four groups in the study, a total of 216 participants (54 per group) must be enrolled. Based on our previous experience, a dropout rate of 16% was expected; to account for this, we aim to recruit a total of 256 participants, with 64 participants per group.

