### Primary analysis

GEE Framework: The primary outcome, psychological distress as measured by the K10 scale, will be analyzed using the GEE framework. Robust standard errors will be used to account for correlated data due to repeated measures. An exchangeable correlation structure will be assumed.Primary Comparisons: Comparisons will be made between each intervention group (Gita, Kuchipudi, and Both) and the control group. Within each intervention group, comparisons over time (pre-intervention, immediate post-intervention, 40 days post-intervention, and 1-year post-intervention) will be performed.Pairwise Post-Hoc Comparisons: Pairwise post-hoc comparisons will be conducted following significant GEE results to identify specific group differences. The Bonferroni correction will be applied to control for the risk of type I error in these multiple comparisons.

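### Row 4 of Table 1 needs the combined arm to beat both single interventions but prints the power of one contrast: a stated 80% becomes about 69% at one visit, and less if the Bonferroni rule applies

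*Protocol article*

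**What the plan says.** In the protocol article, Table 1, row 4 (added benefit), the cells do not describe the same rule.

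- **Question:** "Does learning the Bhagavad Gita provide any added benefit to people experiencing homelessness who are engaging in a recreational activity". This concerns Both v Kuchipudi only.
- **Hypothesis:** the decrease in K10 "will be significantly larger in the Both group than the Bhagavad Gita and Kuchipudi dance groups", at each of the three follow-ups. This takes in Both v Gita and Both v Kuchipudi.
- **Sampling plan:** 54 per group, "for 80% power and 5% alpha".
- **Interpretation:** "If the reduction in the Kessler psychological distress scale scores is highest in the Both group", then an added benefit is suggested. Significance is not mentioned.

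Sample size calculation derives the 54 per group for one 7-point difference between groups. Data analysis sets the threshold: "Statistical significance will be set at a two-tailed p < 0.05". Primary analysis names the comparisons with control as primary and then adds "Pairwise post-hoc comparisons will be conducted following significant GEE results to identify specific group differences", followed by "The Bonferroni correction will be applied to control for the risk of type I error in these multiple comparisons". The number of comparisons in that family is not given, and row 4 is neither exempted nor given a family of its own.

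**The concern.** A claim that needs two significant results is harder to reach than either result alone, so a power figure computed for one contrast cannot be the power of the pair. Row 4 prints it as if it were. This holds whatever is done about multiplicity.

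The multiplicity rule adds a second uncertainty. Both v Gita and Both v Kuchipudi are not among the named comparisons with control, so they appear to fall into the pairwise post-hoc set and under its Bonferroni correction. How much that costs depends on a family size that the plan leaves open.

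At stake is the reading of a negative row 4. Readers told that the trial had 80% power for this question would take a failure to show added benefit as fairly informative. Under the hypothesis as worded, a true 7-point advantage over each single intervention would be missed about three times in ten without correction. With a six-pair correction it would be missed about six times in ten.

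**Working it through.** **The plan's own figure.** Sample size calculation gives V_eff = 55/(1 + 3 × 0.5), which is 55/2.5 = 22.0; the text prints 22.5. With 22.5 the printed formula gives 2.80² × 22.5/(7² × 0.5²) = 176.4/12.25 = 14.4, not 53.3. No SD appears. In a plain two-group comparison, 54 per group gives 80% power for 7 points only if the SD is about 7 × √27/2.80 = 13.0; an SD of 10 gives 95%, 12 gives 86% and 15 gives 68%. I therefore take 80% per contrast as given, and everything below is conditional on it.

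**Inputs.**
- Two-sided 0.05 (Data analysis).
- 80% power for 7 points in one contrast (Sample size calculation), so the expected z-statistic is 1.96 + 0.84 = 2.80.
- 1:1:1:1 allocation (Participants). With n per arm and common variance σ², each contrast has variance 2σ²/n. The two contrasts share the Both arm, so their covariance is σ²/n and their correlation is 0.5.
- A true advantage of 7 points over each single intervention.

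**Joint power at one visit.** This is the bivariate normal probability that both z-statistics exceed the critical value c, that is Φ₂(2.80 − c, 2.80 − c; 0.5). The family size m is an assumption: 2 is row 4's own pair, 6 is all pairs of four groups, and 18 is six pairs at three follow-ups.

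| m | level per test | c | one contrast | both contrasts |
|---|---|---|---|---|
| 1 (no correction) | 0.05 | 1.960 | 80.0% | 68.7% |
| 2 | 0.025 | 2.241 | 71.2% | 57.2% |
| 6 | 0.00833 | 2.638 | 56.5% | 40.1% |
| 18 | 0.00278 | 2.991 | 42.5% | 26.1% |

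The requirement of a significant GEE result before pairwise testing is ignored here; it could only lower these figures.

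**False-claim rate when both wins are required.** The worst case is one contrast null and the other very large. The chance of a false claim in favour of Both is then P(Z > 1.96) = 2.5%. If all groups are equal it is 0.46%. At 0.05/6 per test the worst case is 0.05/12 = 0.42%. Taken alone, the joint claim is controlled without any division.

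**The three visits.** The hypothesis covers all three follow-ups, so the visit rule matters. I assume change scores correlated 0.5 between visits and no correction.
- Both contrasts required at all three visits: joint power is 44.5%, roughly 45%.
- A joint win at any visit suffices: the worst-case false-claim rate in favour of Both is 1 − Φ₃(1.96, 1.96, 1.96; 0.5) = 6.3%, so the 2.5% bound no longer holds.

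**The case against.** The strongest reply is that the plan fixes no both-must-win rule. Only the hypothesis cell requires two wins; the question needs Both v Kuchipudi alone, and the interpretation needs only the largest reduction. If the question governs, row 4 is one contrast and the printed power at least matches its form. That stands as a reason to reconcile the cells first. It does not rescue the row as printed, since the hypothesis is what the power figure sits beside.

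A reader might infer that the plan wrongly corrects row 4 as if either win were enough, and so cuts its power from 69% to 40%. The document does not support that. The Bonferroni rule is written for pairwise comparisons in general. That family also serves the Gita v Kuchipudi question in row 2, and testing all six pairs uncorrected would give a familywise error of about 20% if the groups were equal. The correction is ordinary practice there. It is unnecessary only for the joint claim taken by itself, and the 40% holds only for an assumed family of six.

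It is also fair to say that row 4 is not among the primary comparisons, and that 69% is no better founded than the 80% it starts from. Both points stand. They limit the weight of the finding and require every figure to be labelled conditional. They do not change the fact that the power of two wins is below the power of one.

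**Conclusion.** The point holds in a limited form. Row 4's stated power does not belong to its stated hypothesis. Granting 80% per contrast, equal allocation and a 7-point advantage over each single intervention, the chance of both wins at one visit is about 69% without correction. If the pairwise Bonferroni rule reaches these tests, it is between about 57% and 26%, depending on a family size that the plan does not state. Requiring all three visits lowers the uncorrected figure to roughly 45% under a between-visit correlation of 0.5.

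The general correction is not an error, and no single loss of power can be attributed to it. The comparisons with control are unaffected. The point should be settled before the data are seen, because three cells of one row currently allow three different conclusions from the same results.

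**What to change.** 1. Reconcile row 4's question, hypothesis and interpretation into one decision rule, at one named visit. If the aim is what Gita adds to a recreational activity, the rule is Both v Kuchipudi alone.
2. If both wins are required, state it as an intersection-union claim: Both v Gita and Both v Kuchipudi each significant in favour of Both at two-sided 0.05 at the named visit, with no Bonferroni division for that joint claim. Either contrast reported singly, and any other visit, stays in the corrected pairwise family. State that family's size.
3. Replace the 80% in row 4 by the joint figure for the chosen rule: about 69% at one visit, or roughly 45% if all three visits are required with change scores correlated 0.5. Label it as conditional on 80% per contrast.

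This costs a few cells of one table row and a sentence or two in Primary analysis. The printed power becomes less favourable. Results will also need careful reporting: with p = 0.03 for both contrasts the joint claim would be met, while neither contrast would be significant singly in a six-pair family (0.05/6 = 0.0083). The report should explain that in advance.

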Does learning the Bhagavad Gita reduce psychological distress in people experiencing homelessness	The immediate post-intervention, delayed post-intervention, and long-term follow-up Kessler psychological distress scale scores will be significantly lower than baseline Kessler psychological distress scale scores	54 participants each in the Bhagavad Gita group, Kuchipudi dance group, Both Bhagavad Gita and Kuchipudi dance group, and Control group for 80% power and 5% alpha	The within-group differences will be analysed by repeated measures analysis of covariance, with continued practice and religion as covariates. Subgroup analyses will be conducted by stratifying the participants in each group by age, religion (Hindu, Non-Hindu), educational attainment, and employment. Post-hoc power analyses will be conducted to verify the robustness and reliability of the subgroup analyses	If we find significant within-group differences in the Kessler psychological distress scale scores, it would suggest that learning the Bhagavad Gita has a potential impact on reducing psychological distress in people experiencing homelessness. Additionally, if our subgroup analyses reveal significant differences based on age, religion, educational attainment, and employment, it would imply that the intervention’s effectiveness varies across these subgroups

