Is learning the Bhagavad Gita better at reducing psychological distress than engaging in a hobby in people experiencing homelessness	The decrease from baselines to immediately post-intervention, delayed post-intervention, and long-term follow-up Kessler psychological distress scale scores will be significantly larger in the Bhagavad Gita group than in the Kuchipudi dance group	54 participants each in the Bhagavad Gita group, Kuchipudi dance group, Both Bhagavad Gita and Kuchipudi dance group, and Control group for 80% power and 5% alpha	Intergroup differences will be analysed by the generalised estimating equation and analysis of covariance with continued practice and religion as covariates. Subgroup analyses will be conducted by stratifying the participants in each group by age, religion (Hindu, Non-Hindu), educational attainment, and employment. Post-hoc power analyses will be conducted to verify the robustness and reliability of the subgroup analyses	If our hypothesis holds true, it would suggest that learning the Bhagavad Gita is more effective at reducing psychological distress than engaging in a hobby for people experiencing homelessness. By conducting subgroup analyses, we will further investigate if the effectiveness of the intervention varies based on age, religion, educational attainment, and employment

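### Table 1, row 4: the hypothesis requires a significantly larger K10 reduction in the Both group, but the interpretation rule asks only that it be the highest

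*Protocol article*

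**What the plan says.** All of this is in the Protocol article.

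- **Table 1, row 4, hypothesis.** The decrease from baseline at the three follow-ups is to be "significantly larger in the Both group than the Bhagavad Gita and Kuchipudi dance groups".
- **Table 1, row 4, analysis plan.** "Intergroup differences will be analysed by the generalised estimating equation and analysis of covariance with continued practice and religion as covariates".
- **Table 1, row 4, interpretation.** "If the reduction in the Kessler psychological distress scale scores is highest in the Both group, it would suggest" that the combination may offer additional benefits over either intervention alone. The next sentence drops the hedge: "This finding would indicate that the combination of the intervention has a more substantial effect on decreasing distress levels".
- **Table 1, rows 1 to 3, interpretation.** Row 1 begins "If we find significant within-group differences in the Kessler psychological distress scale scores, it would suggest". Row 2 begins "If our hypothesis holds true, it would suggest that learning the Bhagavad Gita is more effective at reducing psychological distress". Row 3 is also conditional on its hypothesis holding. The hypotheses of rows 2 and 3 each require a significantly larger decrease.
- **Data analysis, and Primary analysis in the SAP section.** Significance is two-tailed p < 0.05, and pairwise post-hoc comparisons are Bonferroni-corrected. The Primary analysis section makes the pairwise comparisons follow a significant GEE result. It lists as primary only each intervention group against control, and change over time within each intervention group.

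**The concern.** The interpretation column of Table 1 is where the protocol commits in advance to what each result will mean, and the Timeline section describes the work as a registered report. A rule there should not be weaker than the hypothesis it is meant to settle.

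The row 4 rule is a rank order. One of the three active arms must always rank first in observed means, whether or not the arms differ. Nothing in the cell separates a real advantage from the arm that came out ahead by chance, and its last sentence states the conclusion firmly.

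The contrasts that would make this separation, Both versus Gita and Both versus Kuchipudi, are not in the listed primary comparisons. In the SAP section they rest on post-hoc tests that follow a significant GEE result. If that condition is not met, those tests are not run, but the observed means can still be ranked. At stake is a claim of added benefit that the trial's own analysis might not support, in results that are to be shared with policymakers and with people experiencing homelessness.

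**Working it through.** The plan states no error rate for the row 4 rule, so there is no figure to reproduce. The check compares the rule as written with the rule that the row's hypothesis implies.

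**Step 1. The rows side by side.**

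| Row | Condition in the interpretation cell | Significance required? |
|---|---|---|
| 1 | Significant within-group differences | Yes, stated |
| 2 | Hypothesis holds (significantly larger decrease) | Yes, through the hypothesis |
| 3 | Hypothesis holds (significantly larger decrease) | Yes, through the hypothesis |
| 4 | Reduction highest in Both | No |

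Row 4 is the only one that does not lead back to a test.

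**Step 2. Inputs.**
- Three active arms of equal size, from 1:1:1:1 allocation (Participants section).
- 54 per arm and correlation 0.5 between repeated measures (Sample size calculation).
- Two-tailed 0.05 (Data analysis).
- Null case: the three active arms have equal true mean reductions and equal variance. The document gives no K10 SD, but the probabilities in Steps 3 and 4 do not depend on one.

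**Step 3. Ranking rule at one visit.** Let D1 be the mean reduction in Both minus that in Gita, and D2 that in Both minus that in Kuchipudi. They share the Both mean, so under the null they have correlation 0.5. Both ranks first when D1 > 0 and D2 > 0:

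P = 1/4 + arcsin(0.5)/(2π) = 0.25 + 0.5236/6.2832 = 0.25 + 0.0833 = 0.333.

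Simulation with 54 per arm and correlation 0.5 (400,000 trials) gives 0.334 at each of the three visits. If Control is ranked as well, symmetry gives 1/4, and the simulation gives 0.249 to 0.251.

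**Step 4. Rule implied by the hypothesis, at one visit.** Both must be significantly better than each single arm, so Z1 > 1.96 and Z2 > 1.96, again with correlation 0.5. Simulation (2,000,000 draws) gives 0.0046, or about 0.5%. This is at the uncorrected level; a Bonferroni correction would make it smaller.

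**Step 5. Comparison.** 0.333/0.0046 ≈ 72. At one visit under the null, the rule as written favours Both about 70 times as often as the rule in the same row's hypothesis.

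**Step 6. More than one visit.** The cell does not say at which follow-up the reduction must be highest. In the three-arm simulation, Both ranks first at all three follow-ups with probability 0.116, and at one or more with probability 0.58. The hypothesis names all three follow-ups jointly, so the text does not support an any-visit reading. The single-visit 33% is the figure to quote.

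**The case against.** The strongest reply is that row 4 should be read across. Its hypothesis cell demands significance, its analysis cell plans GEE and ANCOVA, and the analysis sections set a two-tailed 0.05 level with Bonferroni-corrected pairwise tests. On that reading, *highest* is loose shorthand, and the first sentence of the interpretation is hedged. Most of this stands. It shows that a test is intended, and it means the 33% describes the cell taken alone. It does not show that the cell says so. Rows 1 to 3 make the link to significance and row 4 does not, the hedge is gone by the second sentence, and the cell refers to none of the planned tests.

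Three stronger readings are tempting, and the documents do not support them.

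- **The trial has a false-claim rate of one third by construction.** That would require the team to set aside its own hypothesis and its planned tests.
- **The rate is 58%.** That assumes success at any one of three visits, which the row does not state.
- **The conclusions are defective because no row uses the 7-point difference.** The Sample size calculation section uses 7 points as the difference the trial is powered "to detect a minimum clinically significant difference of 7 points between the groups using GEE". A design difference need not be a decision threshold. In any trial with 80% power at two-sided 5%, an observed difference of about 1.96/2.80 = 70% of the design difference reaches significance. Any other percentage here would rest on an assumed K10 SD, because none is given. Rows 2 and 4 speak of greater effectiveness and additional benefit, not of clinical significance.

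**Conclusion.** The concern holds as an internal inconsistency confined to row 4 of Table 1. The hypothesis requires a significantly larger reduction in Both than in each single-intervention arm, while the pre-stated conclusion requires only that Both rank first.

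Taken literally, the conclusion rule favours Both about 33% of the time at one visit when the three active arms are equal, against about 0.5% under the row's own hypothesis. Both figures assume equal arm sizes and equal variances, and the second uses the uncorrected two-sided 0.05 level. They describe the wording of the cell, not the expected conduct of the trial, because the planned pairwise tests would reduce the risk if they are applied before the conclusion is drawn.

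Rows 1 to 3 are not affected. The lack of any reference to 7 points in Table 1 is a matter of interpretive context, not a contradiction. Severity is moderate to minor: the stated rule should be corrected, but no test, sample size or data collection is undermined.

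**What to change.** In the interpretation cell of Table 1, row 4, replace the condition that the reduction is highest in Both with: the reduction is significantly larger in the Both group than in the Gita group and than in the Kuchipudi group, with the adjusted difference and a confidence interval excluding zero for each, at the planned corrected level. Make the final sentence of the cell, on a more substantial effect, conditional on the same result.

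Optionally, report the estimates and intervals alongside the 7-point difference from the Sample size calculation section, as context and not as a decision threshold.

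The cost is table wording only, with no extra data. The downside is that a less favourable headline is possible: Both may rank first and still not support a claim of added benefit. The change is best made before results are known.
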